
### Participants' Eligibility and Data Collection

The target study population is Black men between the ages of 30 and 80 years in Northeast FL. Being a community engagement research project, the target populations will be fully engaged at each stage of the research implementation. Thus, there is likely to be a modification to the proposed strategy based on input from the working group and CAB at each site. The prostate health REACH services at each site will be promoted through active and continuous community engagement and outreach led by CHWs. Black men residing near the intervention ALPs will be targeted to access the services.

### Participants Recruitment

Figure 5 provides a summary of the data collection steps. For the adoption and program implementation, our goal is to recruit a total of 150 early adopters and users for the program (50 per site) and 50 participants at the comparison Post. Participants are actively recruited by CHWs safely through door-to-door visits, introducing the CoLLab REACH services, or dropping off information about the CoLLab Health System. We also partnered with local media to introduce the CoLLab Health System. Each site had a Grand Opening date, with community members invited to the Grand Opening. The participants will be followed over a minimum of one year.

**Figure 5. F5:**
[figure not shown]
Community living lab study research design. CoLLab: Community Living Lab; REACH: Resources, Education, Amenities, and Community Health.

### Study Timelines

The participants at intervention sites will be asked to visit their respective CoLLab Health System site at least twice a month and up to 24 times over one year to use any of the services. Additionally, the CoLLab sites will be open to the public. Data will be collected in-person or by phone 4 times over one year, at baseline and every 4 months (months 4, 8, and 12).

### Data Collection, Assessment, and Evaluation Plan

The CoLLab Health System sites will operate similarly to any support service center. A CHW will be on site to welcome Black men and provide an overview of the services that are available. S/he will then provide an intake form for the participant to state the kind of services they would like to access. The intake form will ask for first name, race, ethnicity, birth year, and residential zip code. Additionally, participants will check services that they would like from a list. Subsequently, the services will be provided or made available to the participant. Regardless of the service (even use of a computer to access cancer information), participants will be required to complete the intake form to capture use. Data will be collected in-person or by phone 4 times over one year, at baseline and every 4 months. At each stage, the data collection steps are as follows:

Informed consent will be secured by the interviewer prior to data collection.The survey data will be collected using REDCaP, a web-based, clinical data-capture tool available for any research project at Mayo Clinic.Pretest survey will be administered at enrollment for both intervention and comparative group participants.Follow-up survey will be conducted every 4 months, with data collected a total of 4 times.A US $20 incentive will be provided to all participants for each survey administration.

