#### Additional Program Assessment

Additional program evaluation will include (1) assessing the reach of the CoLLab Health System prostate health REACH services*,* including extent and patterns of use, number of people reached over the period of the intervention, and demographics of people reached; and (2) the number of people who were successfully navigated for SDOH, clinical trials, and health care. The information from both individual-level and community-level assessments will be used to refine the services.

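### The form named as the record of service use is filled in before any service and lists what men would like, so it records visits and requests, not receipt

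*Protocol article*

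**What the plan says.** The protocol article, under Data Collection, Assessment, and Evaluation Plan, describes a visit in a fixed order. A CHW welcomes the man and outlines what is on offer. The CHW then hands over an intake form "for the participant to state the kind of services they would like to access". The form takes a few personal details, and "participants will check services that they would like from a list". The next step is: "Subsequently, the services will be provided or made available to the participant". The section then gives the form its measurement role: whatever the service, even use of a computer, "participants will be required to complete the intake form to capture use".

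Study Timelines asks men at the intervention sites to visit at least twice a month, up to 24 times in a year, "to use any of the services".

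Additional Program Assessment lists two groups of results. The first is reach, including "extent and patterns of use, number of people reached over the period of the intervention". The second is "the number of people who were successfully navigated for SDOH, clinical trials, and health care". The Discussion (Principal Findings) presents the tracking of service use as one of the features that will show how the sites function.

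**The concern.** A form completed before a service, listing what is wanted, is a record of demand. The article names it as the record of use. A ticked service may not be given that day, or may only be made available. A service may also be given without having been ticked.

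What is at stake is a feasibility result. The primary objective, stated in the Introduction, is whether the sites can open up access to the prostate health services. How much each service was used is direct evidence on that. The programme assessment is also meant to guide refinement of the services. If a requested but undelivered service appears as used, the gap that a learning health system should find stays hidden.

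The mix of services adds to this. They range from food, housing and legal help to prostate cancer education and clinical-trials matching, while the individual outcomes concern prostate cancer and clinical trials. If those outcomes do not move, the team will want to know whether the education failed or was never received. Ticks alone cannot answer that.

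**Working it through.** No figure in the article bears on this point, so the check sets its statements side by side.

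1. **Timing.** In the data collection section the form comes first and the service follows. An entry made before the service cannot record its completion.
2. **Content.** The list is of services the man would like ("Additionally, participants will check services that they would like from a list"). The other fields are first name, race, ethnicity, birth year and zip code. No field for delivery is described.
3. **Link from tick to receipt.** The services are then provided or made available. The second alternative means that a tick need not end in a service received.
4. **Declared purpose.** The same form is the one instrument named for capturing use.
5. **Where the data go.** Additional Program Assessment reports the extent and patterns of use. It names no other source.
6. **Other possible sources.** Textbox 1 lists fidelity among the process indicators, Study Overview promises assessment of implementation fidelity, and the Individual Assessment section collects satisfaction and perceived quality from intervention participants. None of these is described as a record of which service was delivered at which visit.
7. **Role in the outcome analysis.** Statistical Analyses compares the intervention and control groups at each time point and over time. No use or dose variable enters.

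The direction of the error can be examined in symbols. For a given service over a given period, let

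- a = occasions ticked and delivered,
- b = occasions ticked and not delivered,
- c = occasions delivered without a tick.

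Requests are a + b and deliveries are a + c. If requests are read as use, the error is (a + b) − (a + c) = b − c. The article gives none of a, b or c, so neither the size nor the sign of b − c can be derived. If b and c happened to cancel in total, they could still differ service by service, and the patterns of use would be wrong even with a correct total.

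The gap between request and receipt probably varies by service. For a video or a computer on site, the two would usually coincide at the same visit. For Wellness Rx, which the article says is offered once a year at each intervention Post, a tick at any of up to 24 visits need not be followed by the service that day.

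**The case against.** The strongest reply is that this is a journal article. Form layouts and CHW logs normally sit in the full protocol or the intervention manual, neither of which is shown, and fidelity monitoring is promised. The requirement to complete the form for every service could also be read as a sign-in for each service accessed.

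Part of this stands. A delivery log may exist; if so, the remedy is simply to name it as the source for use. But the article does more than leave the source out. It names an instrument and describes it as a list of wishes completed beforehand. Even as a sign-in, that form shows attendance and intent, not receipt.

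Several stronger readings are tempting, and the article does not support them:

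- **Each tick counts as one use.** No rule for turning ticks into counts is given.
- **Use is overstated by a definite factor.** This would need the delivered share of requests, which is not reported. Services given without a tick pull the other way, so net overstatement is not shown.
- **The count of men successfully navigated is also invalid.** It is listed separately and not tied to the intake form. Its source is unstated. It covers social needs, clinical trials and health care, so it does not fill the gap for education, videos, Wellness Rx, the support group or advocacy training.
- **Cancer and non-cancer services cannot be told apart.** The tick-list already separates service types. What it lacks is delivery by type.
- **The trial's outcome comparison is biased.** The stated analysis is by group and uses no exposure variable.

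**Conclusion.** The point holds for the programme evaluation. Followed as written, the extent and patterns of use would rest on visits and requests, and could misstate what was delivered by an amount and in a direction that the article does not allow anyone to estimate. The stated comparison between intervention and control groups is unaffected. Any later dose analysis built on the same form would inherit the problem, but none is planned in the article.

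This conclusion assumes that the form is used as the article describes it and that no separate delivery record serves as the source for use. The change is worth making because the result bears on the primary objective and the remedy is cheap. It is not a reason to doubt the outcome analysis.

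**What to change.** Add a field to the existing intake form, completed by the on-site CHW at the end of the visit, that marks each listed service as delivered, referred or not delivered. Base the extent and patterns of use on that field, by service type, with prostate cancer and clinical-trials content shown separately. Report the ticked services as demand, next to use and not in place of it. If a delivery log already exists, name it as the source for use instead.

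Data collection began in October 2024, so the new field can help only the remaining visits. Entries made without a delivery field should be labelled as services requested and not pooled with delivered use.

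The cost is about a minute of CHW time per visit, an estimate that does not come from the article. No extra staff or visits are needed, since a CHW is already on site and the form is already required. Reported use may turn out lower than the request count.

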### Individual Assessment

The individual assessment will survey 200 participants, with 150 recruited at the intervention Posts and 50 recruited at the comparison Post. Using a pretest-posttest design, we will evaluate the impact of the CoLLab prostate health REACH services. In addition to evaluating the impact, we will also use the data and care experiences to improve the services continuously. As this is an exploratory short-term intervention, we will assess short-term goals of knowledge/learning improvement focused on the goals to (1) improve Black men’s CaP awareness, knowledge, attitude, health beliefs, perceived control, intentions, and cues to action; and (2) increase Black men’s clinical trials’ awareness, knowledge, attitude, perceived control, intentions, and cues to action. Using the questionnaire adapted from the validated CaPTC/AC3 Standardized Global Behavioral and Epidemiological Measures for Prostate Cancer Studies in Black Men [36,37]*,* we will collect data at baseline, month 3, 6, 9 and assess changes in (1) CaP-related knowledge, attitude, health beliefs, perceived control, intentions, and cues to action; and (2) clinical trials-related knowledge, attitude, perceived control, intentions, and cues to action. In addition, we will assess how many of the men sign up for the Mayo Clinic Community Research Registry, an indication of their interest in being matched to clinical trials at Mayo Clinic, as well as their participation in clinical trials. The study variables are described below.


Participants in the intervention group will also be asked to provide their satisfaction with and perceived quality of the CoLLab prostate health REACH services. The demographic characteristics of all participants and information on access to medical services will also be assessed.

### Statistical Analyses

Responses obtained from data collection will be analyzed using a PC-SAS program. The internal consistency of the study scales will be calculated to estimate their reliability. For each scale, item-remainder correlation will be assessed for item analysis. To assess the impact of the prostate health REACH services at CoLLab Learning Health System sites on study outcomes, the collected data will be evaluated for data quality and then summarized and analyzed. The data will be summarized using standard descriptive statistics for demographic and outcome variables. At baseline, comparisons of the early adopter group and the comparative group on study variables will be done to assess the similarity of the groups using appropriate tests, such as the *t* test, Wilcoxon test, or chi-square test, and 95% CIs. Generalized linear mixed regression approaches, such as repeated analysis of covariance, logistic mixed-effects regression, or a linear mixed-effects model, based on the types of outcomes, will be considered to study the differences between the study variables for the intervention and control groups. At baseline and months 4, 8, and 12, a direct comparison between the early adopter group and the comparison group will be carried out. In addition, trends in outcome variables for each of the 2 groups will be examined to compare the incremental differences in the outcome variables among the Black men over one year. We anticipate seeing a significant improvement in the study outcomes for the early adopter group at months 4, 8, and 12. Over the one-year intervention period, the trend analyses should show significant differences between both groups.

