**Methods:**

The proposed research design for the study is a pragmatic clinical trial. The research setting is Northeast Florida, with the intervention based in 3 American Legion Posts (ALPs) and the control in one ALP. The development of the CoLLab REACH intervention was guided by the Intervention Mapping Framework, focusing on program design, adoption, implementation, and monitoring and evaluation plan. The intervention was cocreated with community members and is being provided by community health workers. The primary outcomes are improvement of Black men’s CaP awareness, knowledge, attitude, health beliefs, perceived control, intentions, cues to action, and clinical trials’ awareness. Generalized linear mixed regression approaches will be used to determine the differences between the study variables for the intervention and control groups.

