### Study Overview

This study is conducted by members of the iCCaRE Consortium, established in 2022 to address the disproportionate burden of CaP among Black men worldwide through research, research training, community engagement, and outreach (iccareconsortium.org). Four ALPs in Black communities in Florida were selected, with 3 serving as intervention sites (ALPs 197, 244, and 194) and one as a comparative site (ALP 187). The study focuses on the final 3 steps of the Intervention Planning Framework:

Step 3: Program Design – Translating strategies into operational plans, including materials development, design, pretesting, and production.Step 4: Adoption and Implementation Plan – Establishing procedures and structures to support intervention delivery.Step 5: Monitoring and Evaluation Plan – Developing processes for ongoing assessment of implementation fidelity, outcomes, and impact.

The study design is a 30-month, mixed methods, pragmatic clinical trial to evaluate the feasibility, effectiveness, and scalability of this community-based intervention.

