### Research Intervention and Comparator Sites

The research setting is ALPs in Northeast Florida. The Posts selected for this IDEA award are highly active in their communities, located in underserved minority neighborhoods, and primarily have minority veteran members. The CoLLab sites included one Hub in Duval County (Post 197) and 2 Spokes, Posts 244 in Duval County and 194 in St. Johns County. The comparative site was Post 184 in Delan County.

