### Monitoring and Evaluation

#### Community Assessment

The community-level assessment data will be collected through the annual Mayo Clinic Comprehensive Cancer Center Community Cancer-focused Needs Assessment. The Mayo Clinic conducts an annual needs assessment that captures the following variables in the Cancer Center catchment areas, which include both study counties: demographics, health status, health care access, information seeking, and health information access, engagement with Cancer Center, cancer history (personal and family), health behaviors, community attributes, mental health/wellbeing, and clinical trials participation. Participants within the study counties will be purposefully oversampled during the study period. Focusing on the following variables, we will compare the study counties controlling for demographic variables: health status, health care access, information seeking and health information access, cancer history, health behaviors, and clinical trials participation. First, the data will be summarized using standard descriptive statistics for demographic and outcome variables. Subsequently, comparisons of the intervention county (Duval and St. Johns) and the comparative county (Volusia) on study variables will be conducted to assess the similarity of the groups using appropriate tests, such as the *t* test, Wilcoxon test, or chi-square test, and 95% CIs.

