### Limitations

Several limitations warrant consideration. First, as a feasibility trial conducted under controlled conditions, this study is designed to assess efficacy rather than real-world effectiveness; future implementation science studies will be needed to evaluate scalability and sustainability [29]. Participant attrition presents another risk, as differential dropout could compromise group equivalence; however, analytic strategies controlling for baseline characteristics will mitigate this threat. Repeated survey administration may also introduce testing effects, though evidence suggests that spacing assessments reduces this bias [27,30]. Finally, as a community engagement research initiative, some CoLLab components may evolve based on CAB feedback, introducing variability across sites. Such adaptations are consistent with community-engaged research frameworks but may complicate comparisons across intervention sites.

Despite these limitations, this protocol addresses important evidence gaps in CaP inequities research by testing a comprehensive, community-driven model that integrates multilevel determinants—individual, interpersonal, community, and structural. The CoLLab Learning Health System advances current approaches by combining CHW-based navigation, tailored education, digital access, and continuous learning into a scalable framework capable of supporting sustained prostate health equity. If successful, CoLLab may serve as a national model for implementing community-based Learning Health Systems that enhance CaP prevention, early detection, survivorship, and clinical trial participation in marginalized communities.

We recognize that the success of our efforts to address CaP burden depends not only on rigorous research implementation but also on the effective dissemination of findings to both scientific and, critically, lay communities. To ensure broad and meaningful reach, we will implement a structured dissemination strategy coordinated through the iCCaRE Consortium. This strategy will include the publication and public release of community reports summarizing key initiatives and findings; presentations at community health events; and targeted press releases through local Black media outlets.

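### With a single control Post in another county, the intervention effect cannot be separated from that Post, so the plan should not forecast significant group differences or claim efficacy or effectiveness

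*Protocol article*

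**What the plan says.** The Abstract describes the design as a pragmatic trial "with the intervention based in 3 American Legion Posts (ALPs) and the control in one ALP". Study Overview repeats the three-to-one split and calls the study a "pragmatic clinical trial to evaluate the feasibility, effectiveness, and scalability" of the intervention. The Posts were selected by the study team (Research Intervention and Comparator Sites: "The Posts selected for this IDEA award are highly active in their communities"), and no randomisation of Posts or men is described.

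The control Post is in a different county from every intervention Post. The same section states "The comparative site was Post 184 in Delan County", and Community Assessment plans "comparisons of the intervention county (Duval and St. Johns) and the comparative county (Volusia) on study variables will be conducted". Services are designed and adopted Post by Post.

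Statistical Analyses lists baseline similarity tests, generalized linear mixed approaches chosen by outcome type, a direct two-group comparison at baseline and at months 4, 8 and 12, and a comparison of trends. It then forecasts the result: "Over the one-year intervention period, the trend analyses should show significant differences between both groups". It names no fixed or random effects, so Post is neither included nor excluded.

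Limitations says the study is designed to assess efficacy. It covers attrition, repeated testing, and adaptation of components "introducing variability across sites". It mentions neither the single control Post nor clustering.

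**The concern.** The intervention is delivered to whole Posts, and there is only one Post without it. Anything particular to that Post or its county, such as a local campaign, a different way of recruiting, or a different trend in awareness, is part of the estimated intervention effect.

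Calendar time is one concrete route. The Abstract reports that intervention recruitment was complete by June 2025, when the control Post had 11 men and was still recruiting. Later control recruits will therefore be followed in a later period.

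The evaluation of individual-level impact in the second aim rests on this comparison. A significant group difference could be reported as evidence of efficacy when the design cannot tell it apart from a difference between places.

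**Working it through.** **1. What follows from the design alone.** Let the mean change at a Post be (common change) + (intervention effect, if given) + (Post-specific change). The mean of the three intervention Posts minus the control Post estimates

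effect + (average Post-specific change at the three Posts) − (Post-specific change at the control Post).

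The last term is a single unreplicated quantity that no data in the study can estimate apart from the effect. In the direct comparison at one visit, stable differences between Posts enter in the same way. In the trend contrast they cancel, and only Post-specific change over time remains. This step needs no numerical assumption.

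**2. Standard errors if Post is omitted.** The article gives no power, alpha, effect size or ICC, so there is no stated figure to reproduce.

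Inputs:
- Planned numbers, from Participants Recruitment: 3 × 50 = 150 intervention men and 50 control men.
- Assumed: SD = 1; two-sided 5% test; ICC (ρ) of 0.01, 0.02 or 0.05. For trends, ρ is the ICC of change scores.

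Formulas:
- Variance with men treated as independent: 1/150 + 1/50 = 0.02667 (SE 0.163 SD).
- Variance for an effect that generalises beyond these Posts: ρ(1/3 + 1) + (1 − ρ) × 0.02667.
- True type I error: 2[1 − Φ(1.96/√ratio)], where ratio is the second variance divided by the first.

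| ICC | Between-Post part | Within-Post part | Total | Ratio | SE understated by | Type I error |
|---|---|---|---|---|---|---|
| 0.01 | 0.01333 | 0.02640 | 0.03973 | 1.49 | 1.22 | 10.8% |
| 0.02 | 0.02667 | 0.02613 | 0.05280 | 1.98 | 1.41 | 16.4% |
| 0.05 | 0.06667 | 0.02533 | 0.09200 | 3.45 | 1.86 | 29.1% |

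A simulation of a participant-level t test (20,000 runs, four Posts of 50) gave 10.8%, 16.4% and 29.0%. At ICC 0 it gave the nominal 5.0%.

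The Data Collection section gives 195 intervention and 11 control men enrolled. On those numbers the error is 6.5% at ICC 0.01 and 12.6% at 0.05. It is lower only because 11 controls already make the standard error large (0.31 SD). If the control Post reaches 50 (195 v 50), it is 11.2% and 30.2%.

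**3. What including Post can recover.** With the Post as unit, 3 v 1 leaves 4 − 2 = 2 degrees of freedom (critical t = 4.30). All the information on between-Post variance comes from the three intervention Posts. With unlimited men per Post, the SE cannot fall below √(ρ × 4/3) = 0.115, 0.163 or 0.258 SD. For 80% power on 2 df, the non-central t distribution requires an effect of about 5.65 SEs:

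- 5.65 × 0.115 = 0.65 SD
- 5.65 × 0.163 = 0.92 SD
- 5.65 × 0.258 = 1.46 SD

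If the between-Post variance were known, the multiplier would be 1.96 + 0.84 = 2.80 and the floor 0.32, 0.46 or 0.72 SD. It is not known. The smallest p-value from permuting the arm label over four Posts is 1/4 = 0.25.

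**The case against.** A reader might infer that the plan commits to a participant-level model and that its error bars are therefore wrong. The article does not support this. It says mixed approaches will be considered and names no terms, and a condensed article commonly leaves model terms to the full protocol or analysis plan. The t, Wilcoxon and chi-square tests it names are for baseline similarity. The type I error figures are therefore conditional on Post being omitted. They also depend on assumed ICCs and on wanting a conclusion beyond these four Posts. For a contrast confined to the four Posts, participant-level standard errors are appropriate.

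A reader might also infer that any ordinary difference between communities would be reported as an effect. That goes too far: the design is longitudinal, and stable Post differences cancel in the trend contrast that the forecast concerns. It is fair only for the direct comparisons at each visit.

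Finally, the primary objective is feasibility, the intervention is called exploratory, Limitations disclaims real-world effectiveness, and the forecast is an expectation rather than a decision rule. This lowers the severity. It does not remove the point: Limitations still claims efficacy, Study Overview still claims effectiveness, and no unseen analysis plan can separate arm from the only control Post.

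**Conclusion.** The point holds on the design facts. With three selected intervention Posts and one control Post in another county, the effect cannot be distinguished from whatever is peculiar to the control Post: stable differences in the visit-wise comparisons, and Post-specific change in the trend contrast. The forecast of significant differences and the efficacy and effectiveness wording claim more than the design can support, and the limitation is not stated.

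The inflation of type I error to 10.8%, 16.4% or 29.1% is illustrative. It assumes 150 v 50, Post left out of the model, and an ICC of 0.01, 0.02 or 0.05, none of which the article gives. With Post taken into account on 2 df, differences smaller than about 0.65, 0.92 or 1.46 SD cannot be detected with 80% power, however many men are enrolled.

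Given the feasibility and exploratory purpose, this should be fixed but does not invalidate the study.

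**What to change.** In Statistical Analyses:

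1. Fit Post (four levels) by visit in place of a two-level arm term. Report each Post's change from baseline with a 95% CI, then the mean of the three intervention Posts minus the control Post, worded as a contrast between these four Posts only.
2. Delete the expectation of significant between-group differences. State that intervention-versus-control results are descriptive and do not establish efficacy or effectiveness.
3. Optionally, add a Post-level sensitivity interval: contrast ± 4.30 × s × √(1/3 + 1), where s is the SD of change among the three intervention Posts. It assumes the control Post shares that variance. Its half-width is about 5s (4.30 × 1.155 = 4.97), from an SD based on three values, so it will be very wide.

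Elsewhere, align the effectiveness wording in Study Overview with the efficacy wording in Limitations, and add the single-control-Post confounding to Limitations. The control site's identity also needs reconciling, since results by Post will name it: Study Overview gives Post 187, Research Intervention and Comparator Sites gives Post 184 in Delan County, and Community Assessment gives Volusia County.

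The cost is rewording, a small change to the model and a weaker headline claim. None of this removes the confounding; it makes the claims fit the design. No new sites or men are needed. The Abstract says analysis will follow completion of follow-up, so the change can still be specified in advance.
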